**CONFIDENTIAL**

antibody data. Define the IPS for immunogenicity for 3, 6, 9 and 12 months after booster immunization respectively.

**Safety Set (SS):**

It includes all participants who receive one dose of booster vaccination. In immunogenicity analysis, the participant who takes the vaccine erroneously will be included as randomized, and the safety data will be analyzed as treated.

**10.3 Statistical Method****10.3.1 General Considerations**

The measurement data is statistically described with mean, median, standard deviation, maximum and minimum values; Counting data or grade data are expressed in occurrence and frequency. All statistical analysis will be performed by using SAS 9.4 or later version.

CONFIDENTIAL

**10.3.2 Trial completion and demographic characteristics**

The number of participants who are enrolled, completed and discontinued will be summarized in each group. The reason for discontinuation will be analyzed as well. The demographic characteristics will be summarized and described by treatment group.

**10.3.3 Immunogenicity Analysis**

Analysis of covariance (ANCOVA) model will be employed to analyze post-vaccination GMT after logarithmic transformation. In the model, log-transformed GMT after vaccination will be included as dependent variable, pre-vaccination GMT after log-transformation is the covariate and group assignment and booster vaccination time are the fixed effect. The adjusted Least Squares Mean (LSMean) in each arm and difference between the two groups together with 95% confidence interval (CI) will be estimated from the model. After inverse log-transformation, calculate the adjusted GMT after vaccination and the LSMean of GMT ratio between the experimental group and control group together with 95% CI. The reverse cumulative distribution plot is to depict the pre- and post-vaccination antibody data in the experimental and control groups.

CONFIDENTIAL

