### **4.2. Procedures and Methodology**

#### **Sample size:**

A total of 516 healthy participants aged 18 years and above who have been vaccinated with 2/3 doses of inactivated COVID-19 vaccine, will be enrolled, and randomly assigned to the experimental group and control group in a 1:1 ratio, with 258 participants in each booster group.

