#### **4.6 Randomization and Blinding**

**CONFIDENTIAL**

#### **4.6.1 Randomization**

A stratified block randomization method will be employed in the study. Interactive Web Response System (IWRS) will be used in participant randomization and vaccine allocation.

The randomization statistician will produce a participant randomization list and vaccine randomization list by SAS 9.4 (or later version), which will be imported into IWRS by the system engineer. After one participant is screened successfully, the investigator at each centre will log onto IWRS to get the randomization number of the participant. Before vaccination, the investigator will receive the vaccine number from IWRS and inoculate vaccines accordingly. If the vaccine is damaged, the investigator could acquire a new vaccine number from IWRS and inoculate the vaccine with a new vaccine number.

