### **5.1 Participant Population**

#### **5.1.1 Inclusion Criteria**

Individuals are eligible to participate in this study if all of the following criteria apply:

- Age:  $\geq 18$  years;
- Judged by the investigator that the health condition is well after inquiry and physical examination;
- Vaccinated with 2 or 3 doses of inactivated COVID-19 vaccine (Vero Cell vaccine)  $\geq 6$  months prior to study screening and according to product insert;
- Female participants who are not pregnant or nursing or at the time of enrolment (confirmed via negative urine pregnancy test), and do not have plans to become pregnant within the first 6 months after enrollment. Effective contraceptive measures have been taken within 2 weeks before study inclusion and initiation;
- Be able and willing to provide written informed consent to participate in the study and complete all study requirements according to the study protocol.

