**CONFIDENTIAL**

## 10. STATISTICAL CONSIDERATIONS

### 10.1 Sample Size Considerations

#### Primary indicators:

- The antibody GMT (Omicron) in the experimental group was superior to that in the control group 14 days after immunization.
- H0:  $\delta \leq 0.0212$  vs. H1:  $\delta > 0.0212$  (both are logarithmic scale, equivalent to GMT ratio 95%CI > 1.05)

**Calculating basis for sample size:** by referring to the relevant data of this product in ex-China clinical trials, 0.55 (logarithmic scale) is taken as the standard difference in antibody titer of recombinant COVID-19 vaccine (CHO cell). The probability of type I error  $\alpha=0.025$  (one-sided); power  $1-\beta=0.9$ ; superiority margin  $\Delta=0.0212$  (logarithmic scale, i.e. GMT test group/GMT control group  $\geq 1.05$ ); the test group and the control group are designed according to 1:1.

| Test level
(one sided) | Target     | N of each
group | Superiority
margin         | Actual level
of
difference
between
test group
and control
group | SD          | Total N
after
considering
20% drop-
out |
|---------------------------|------------|--------------------|-------------------------------|-----------------------------------------------------------------------------------|-------------|-----------------------------------------------------|
| 0.025              | 0.9 | 166         | 0.0212
(1.05 fold) | 0.200(
1.6 fold)                                                       | 0.55 | 398                                          |
| 0.025                     | 0.8        | 139                | 0.1139
(1.3)               | 0.30
(2 fold)                                                                  | 0.55        | 348                                                 |
| 0.025                     | 0.85       | 158                | 0.1139
(1.3)               | 0.30                                                                              | 0.55        | 396                                                 |
| 0.025                     | 0.9        | 185                | 0.1139
(1.3)               | 0.30                                                                              | 0.55        | 462                                                 |

CONFIDENTIAL

|       |      |     |                |      |      |      |
|-------|------|-----|----------------|------|------|------|

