**Calculating basis for sample size:**

By referring to the relevant data of this product in ex-China clinical trials, 0.55 (logarithmic scale) is taken as the standard difference of the antibody titer of the recombinant COVID-19 vaccine (CHO cell). The probability of type I error  $\alpha=0.025$  (one-sided); power  $1-\beta = 0.9$ ; non-inferiority threshold  $\Delta=-0.17609$  (logarithmic scale, i.e., the lower bound of 95%

CONFIDENTIAL

confidence interval of GMT test group/GMT control group after immunization should be at least 0.67); The test group and the control group are designed according to 1:1.

| Test level (one sided) | Target     | N of each group | Superiority margin         | Actual level of difference between test group and control group | SD          | Total N after considering 20% drop-out |
|------------------------|------------|-----------------|----------------------------|-----------------------------------------------------------------|-------------|----------------------------------------|
| 0.025           | 0.9 | 206      | -0.17609 (2/3 fold) | 0 (1 fold)                                               | 0.55 | 516                             |
| 0.025                  | 0.9        | 262             | -0.17609 (2/3 fold)        | -0.02 (0.95 fold)                                               | 0.55        | 656                                    |
| 0.025                  | 0.9        | 344             | -0.17609 (2/3 fold)        | -0.02 (0.90 fold)                                               | 0.55        | 860                                    |
| 0.025                  | 0.9        | 566             | -0.17609 (2/3 fold)        | -0.07 (0.85 fold)                                               | 0.55        | 1416                                   |

Based on the above considerations and the drop-out rate, it is planned to enroll 516 participants.

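### The primary ANCOVA has no term identified as a randomisation stratum and none for number of prior doses (2 vs 3), which may cost a little precision

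*Protocol*

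**What the plan says.** Section 4.6.1 (Randomization) states: "A stratified block randomization method will be employed in the study". Neither that section nor any other names a stratification factor.

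Section 4.2 (Sample size) describes participants "who have been vaccinated with 2/3 doses of inactivated COVID-19 vaccine", and the inclusion criteria in 5.1.1 also admit either two or three prior doses. The expected mix is not given. Section 7.2.1 has the investigators check vaccination records at screening, so the number of doses is known before randomisation.

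Section 10.3.3 (Immunogenicity Analysis) specifies the primary model for log-transformed titre: "pre-vaccination GMT after log-transformation is the covariate and group assignment and booster vaccination time are the fixed effect". The booster vaccination time term is not defined. Section 10.4 marks subgroup analysis as not applicable, so section 10 makes no other provision for dose number.

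**The concern.** The usual practice is to carry the factors that governed randomisation into the primary model. If a stratum is prognostic and is left out, its variance stays in the residual although the design has already balanced it. The standard error is then overstated and the gain from stratifying is lost.

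Number of prior doses is a natural candidate as a stratum or a covariate. It is objective, fixed before randomisation and already collected, and it separates two differently primed groups. If it was not a stratum, leaving it out keeps the interval valid, but a predictor that could reduce residual variance goes unused.

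What is at stake is the width of the interval for the GMT ratio, which section 4.4 compares with 1.05 for superiority and 2/3 for non-inferiority. Bias and the type I error rate are not at stake.

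**Working it through.** **Inputs from section 10.1.** One-sided alpha 0.025 and power 0.90. For the SD, "0.55 (logarithmic scale) is taken as the standard difference in antibody titer". Superiority margin 0.0212 log10 with an assumed true difference of 0.200. Non-inferiority margin -0.17609 log10 with a true difference of 0. Drop-out 20%.

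**Reproducing the plan's own figure.** n per group = 2 × 0.55² × (1.960 + 1.282)² / 0.17609² = 205.01, rounded up to 206. Then 206 / 0.8 = 257.5, rounded up to 258 per group, or 516 in total. The planned enrolment reproduces.

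**Baseline precision.** With 206 evaluable per group, SE = 0.55 × √(2/206) = 0.0542. The 95% half-width is 1.96 × 0.0542 = 0.1062 log10, that is, a GMT ratio multiplied or divided by 1.277. Superiority power = Φ((0.200 - 0.0212)/0.0542 - 1.96) = 91.0%.

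**Effect of adding a dose term.** The documents give neither the dose mix nor a dose effect, so both are assumed. Let p be the share with three doses and d the difference in log10 post-booster titre between dose groups that remains after adjustment for baseline titre. Take 0.55 as the residual SD without the dose term.

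- Share of residual variance explained: R² = p(1-p)d² / 0.55²
- Ratio of interval widths, with the term to without it: √(1 - R²)

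| Residual d, p = 0.5 | R² | Width ratio | Superiority power, 206 per group |
|---|---|---|---|
| 0 | 0 | 1.000 | 91.0% |
| 0.1 (1.26-fold) | 0.008 | 0.996 | 91.2% |
| 0.2 (1.58-fold) | 0.033 | 0.983 | 91.9% |
| 0.3 (2.0-fold) | 0.074 | 0.962 | 92.9% |

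At d = 0.3 the half-width falls from 0.1062 to 0.1062 × 0.962 = 0.1022 log10 (factor 1.265 instead of 1.277). With a 20:80 mix and d = 0.3 the width ratio is 0.976.

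**Check by simulation.** ANCOVA was run with and without the dose term on 412 participants, with blocks of 4 stratified on dose number and 4,000 replicates per setting. The simulation assumed a within-model SD of 0.5. The ratio of standard errors was 1.000, 0.995, 0.981 and 0.959 for d = 0, 0.1, 0.2 and 0.3. Coverage of the 95% interval without the term was 94.8% to 96.0%, so leaving it out does not invalidate the interval.

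**If dose number was not a stratum.** At a 50:50 mix, the between-arm difference in the three-dose share has SD √(2 × 0.25/206) = 0.049. A chance imbalance of 1.96 SD with d = 0.3 moves the estimate by 1.96 × 0.049 × 0.3 ≈ 0.029 log10. The standard error already allows for this on average. A prespecified dose term would remove it from the estimate.

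**The case against.** A reader might infer that the ANCOVA omits the stratification factors outright. The protocol does not support that. It names no factor, and the undefined booster vaccination time term could be one, for example the interval since the last dose. What can be said is that no term is identified as a stratum. The absence of a term for dose number is plain only if the undefined term does not itself stand for dose sequence, which is one more reason to define it.

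A reader might also infer that the standard error is certainly overstated. That needs the omitted factor to have been a stratum and to predict titre beyond baseline titre. The protocol establishes neither for dose number. If dose number was not a stratum, the interval is correct and at most slightly inefficient.

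Larger gains can be obtained by putting raw gaps of 0.2 to 0.4 log10 between dose groups (30 to 50% in one group) over the full planning variance of 0.3025. This gives variance shares of 0.028 to 0.132 and intervals 1.4 to 6.8% narrower. The arithmetic is right. But the model already adjusts for baseline titre, which may carry much of the priming difference, and that range leaves out no effect at all.

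Finally, the names of strata and the complete list of covariates are often left to a statistical analysis plan, which may exist here but is not at hand. That excuses the unnamed strata. It does not fully answer the point on the model: section 10.3.3 states the model term by term, so further factors added elsewhere would depart from the protocol text.

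**Conclusion.** The point holds as a modest, free improvement and not as the correction of an invalid analysis. Randomisation is stratified, and the stated primary model contains no term identified as a stratum and none labelled as number of prior doses. Whether this costs precision depends on a prognostic effect beyond baseline titre that the documents do not give.

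For residual effects of 0 to 0.3 log10 and a 50:50 dose mix, the cost is an interval about 0 to 4% wider than it need be, and at most about 2 percentage points of superiority power (91% against 93%). These figures assume 206 evaluable per group and a residual SD of 0.55. The planned 516 is unaffected, and the interval without the extra terms remains valid.

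**What to change.** Before unblinding, amend section 10.3.3 so that the ANCOVA keeps log10 baseline titre and group, and adds the IWRS stratification factors and number of prior doses (2 vs 3) as fixed effects. Name the stratification factors in 4.6.1. State what booster vaccination time means, so that a stratum is not entered twice under two names. If dose number is itself a stratum, one term serves both purposes.

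The cost is a few sentences. Prior vaccination is already checked at screening and the strata are held in IWRS, so no new data are needed. The dose term uses one degree of freedom out of about 410. The strata use a number that depends on how many there are, which the protocol does not say. The change should be made while the trial is blinded, because covariates chosen after unblinding are open to challenge.

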#### **10.3.4 Safety Evaluation**

Adverse events and serious adverse events will be coded using the Medical Dictionary for Regulatory Activities (MedDRA), and summarized by System Organ Class (SOC) and Preferred Term (PT). AEs will be summarized by solicited and unsolicited AEs as well. The Treatment Emergent Adverse Events (TEAEs) will be analyzed here. AEs occurring before vaccination will be listed.

All TEAEs, vaccine-related TEAEs, vaccine-unrelated TEAEs, Grade  $\geq 3$  TEAEs and vaccine-related Grade  $\geq 3$  TEAEs will be summarized by group. The frequency, participants and percentage in each group will be reported. Fisher exact test will be used to compare the difference between the groups. The strat time and severity of TEAEs will be summarized. The vaccine-related TEAEs and vaccine-unrelated TEAEs will be listed.

All TESAE, vaccine-related TESAEs and vaccine-unrelated TESAEs will be summarized by group. The frequency, participants and percentage in each group will be reported. Fisher exact test will be used to compare the difference between the groups. All TESAEs will be listed.

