### 4.3. Study Endpoint

**CONFIDENTIAL**

**Primary Endpoints:**

1. GMT and the 4-fold rise rate of anti-omicron neutralizing antibody 14 days after a single dose of the booster vaccine in adults  $\geq 18$  years of age.
2. The incidence and severity of any adverse reactions/events within 30 minutes after vaccination;
3. The incidence and severity of solicited adverse reactions/events within 0-7 days after vaccination;
4. The incidence and severity of unsolicited adverse reactions/events within 8-30 days after vaccination;
5. The incidence of SAE and AESI observed after vaccination and up to 12 months after full course of immunization.

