**CONFIDENTIAL**

respectively, the participants were followed-up by telephone and guided to observe the adverse events correctly and fill in the diary card.

3. On the 14th day after vaccination, the investigator reviews the filling of the diary card during this period and re-collect the diary card.
4. On the 8th -28th day after vaccination, the investigator uses telephone follow-up once a week, combined with an active report of the participants to monitor the safety.
5. When it is known that the participant has adverse reactions/events of Grade 3 or above, a face-to-face visit should take place within 24 hours.
6. SAEs and AESIs are observed from the first dose to 12 months after the full course of vaccination via monthly telephone follow-up calls and self-reports from the participants.
7. Participants should contact the doctors on informed consent form/diary card immediately if developed any COVID-19 like symptoms.

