#### **10.7 Handling of Missing Data**

In FAS immunogenicity analysis, LOCF (Last Observation Carried Forward) method will be used to impute the missing values in antibody data after vaccination. And other immunogenicity endpoints will be derived from the imputed data. The missing data in safety and immunogenicity persistence evaluation will be not imputed.

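### The 12-month SAE incidence is summarised only as a crude percentage, which in effect counts participants lost without an event as event-free for the year; a follow-up-adjusted estimate should stand beside it

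*Protocol*

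**What the plan says.** Section 4.3 lists as primary endpoint 5: "The incidence of SAE and AESI observed after vaccination and up to 12 months after full course of immunization". Section 7.3.1 sets the matching observation period, "SAEs and AESIs are observed from the first dose to 12 months after the full course of vaccination", through monthly telephone calls and self-report. Under section 5.1.3, early withdrawal means leaving the study for good.

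For treatment-emergent SAEs, section 10.3.4 states: "The frequency, participants and percentage in each group will be reported". The comparison is also fixed: "Fisher exact test will be used to compare the difference between the groups". No person-time rate, cumulative incidence or censoring rule is named. The section neither states the denominator of the percentage nor gives a summary of AESIs.

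Section 10.2 defines the Safety Set without a minimum follow-up: "It includes all participants who receive one dose of booster vaccination". Section 10.7 adds: "The missing data in safety and immunogenicity persistence evaluation will be not imputed".

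Drop-out appears only in section 10.1. There it inflates the sample size for the day-14 antibody comparisons (column "Total N after considering 20% drop-out") and leads to the planned total: "Based on the above considerations and the drop-out rate, it is planned to enroll 516 participants".

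**The concern.** A crude percentage suits the 30-minute and 0-7 day endpoints, where almost everyone is observed for the whole window. It suits a 12-month incidence less well. SAEs are found through contact with the participant, and that contact can be expected to end at withdrawal. On the natural reading of sections 10.2, 10.3.4 and 10.7 together, someone who leaves at month 3 without an event stays in the denominator as if followed to month 12, while any later event is unseen. Under this method unseen events can only lower the reported figure.

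At stake is the absolute 12-month SAE incidence, which is part of a primary endpoint. The comparison between groups would be affected only if the amount or timing of loss differed between them.

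**Working it through.** **1. The plan's own figure.** Inputs from section 10.1 (non-inferiority table): one-sided alpha 0.025, power 0.9, margin 0.17609 and SD 0.55 on the log10 scale, true difference 0, allocation 1:1.

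n per group = 2 × (1.960 + 1.282)² × 0.55² / 0.17609² = 205.01, rounded up to 206. With 20% drop-out, 206 / 0.8 = 257.5, rounded up to 258 per group and 516 in total. This reproduces the plan. It also shows what the 20% is for: keeping 206 participants per group evaluable for an antibody comparison. It is not a forecast of loss from 12-month safety follow-up.

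**2. Bias of the crude percentage.** Let p be the true 12-month risk, d the share lost, T the time of loss in months and F the cumulative risk by a given time.

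Expected crude percentage = (1 − d) × p + d × E[F(T)].

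With a constant hazard, small p and loss unrelated to risk, F(T) ≈ p × T/12, so

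relative understatement ≈ d × (1 − E[T]/12).

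The protocol gives neither the SAE risk nor the amount and timing of safety loss. All values of d, T and p below are assumptions.

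| Assumed loss | Calculation | Understatement | A true 2.0% reads as |
|---|---|---|---|
| 20%, all at time 0 | 0.20 × 1 | 20% | 1.60% |
| 20%, all at day 14 | 0.20 × (1 − 14/365) | 19.2% | 1.62% |
| 20%, uniform over 12 months | 0.20 × 0.5 | 10% | 1.80% |
| 20%, all at month 9 | 0.20 × 0.25 | 5% | 1.90% |
| 20%, all at month 11 | 0.20 × 1/12 | 1.7% | 1.97% |
| 20%, all at month 12 | 0.20 × 0 | 0% | 2.00% |
| 10%, uniform | 0.10 × 0.5 | 5% | 1.90% |
| 5%, uniform | 0.05 × 0.5 | 2.5% | 1.95% |

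**3. Front-loaded events.** Suppose half of the events fall in month 1 and the rest are spread evenly over months 2-12. With uniform loss, the mean of F(T)/p is (1/12) × 0.25 + (11/12) × 0.75 = 0.708. The understatement at 20% loss is then 0.20 × (1 − 0.708) = 5.8%, against 10% under a constant hazard.

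**4. Between groups.** Equal loss scales both percentages by the same factor, so their ratio is almost unchanged. With an assumed uniform loss of 20% in one group and 10% in the other, and equal true risks, the ratio is 0.90 / 0.95 = 0.947.

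**5. In participants.** At an assumed 2%, 258 × 0.020 = 5.2 participants per group have an SAE. The crude method would show 258 × 0.018 = 4.6 (uniform 20% loss) or 258 × 0.0162 = 4.2 (all lost at day 14). The shortfall is half to one participant per group. For comparison, the exact 95% CI for 5/258 runs from 0.6% to 4.5%.

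**The case against.** The strongest defence is that participants and percentage of the vaccinated set, with Fisher's exact test and a full listing of SAEs, is a usual and legitimate descriptive summary. The endpoint refers to events observed, and a crude percentage answers that directly. Exposure-adjusted tables, denominators and AESI displays are often left to a statistical analysis plan, which is not at hand. No hypothesis, sample size or suspension rule rests on the 12-month SAE incidence. At a 2% incidence the error is far smaller than the sampling uncertainty. Section 10.3.2 also summarises discontinuations and their reasons, so a reader could see an imbalance.

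Most of this stands, and it limits the weight of the point. It does not remove it: section 10.3.4 does not leave the SAE summary open but names the measure and the test, and that measure is biased in a known direction for a 12-month incidence.

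A reader might go further and infer that the plan's own 20% drop-out means the incidence will be understated by 10-19%. The protocol does not support that. The 20% belongs to the day-14 antibody comparison, and a participant without a valid day-14 sample can remain in safety follow-up. Further, 10-19% covers only uniform to very early loss; late loss or front-loaded events give less.

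A reader might also infer that the group comparison is tilted. That needs unequal loss, and nothing in the protocol predicts it for a double-blind, single-dose trial.

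**Conclusion.** The point holds as a cheap improvement. As written, the 12-month SAE incidence is biased downward by an amount that depends on how many participants are lost and when. If 20% loss is assumed, with a constant hazard and loss unrelated to risk, the relative understatement is 0-20%, and about 10% if loss is uniform. With less loss, or with events concentrated early, it is smaller. In a group of 258 at an assumed 2% risk, this is at most about one participant. The between-group ratio is almost unaffected unless loss differs between groups.

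Two links are readings rather than statements of the protocol. The denominator is inferred from the Safety Set definition. For AESIs the method is inferred as well, because section 10.3.4 does not mention them; the point is firm for SAEs only.

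**What to change.** In section 10.3.4, for the 12-month SAE endpoint and likewise for AESIs, add one of these beside the crude percentage and Fisher's test:

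- participants with a first event per 100 person-years of observed follow-up, counted from the booster to the first event, last safety contact or month 12, with an exact Poisson 95% CI per group and the rate ratio; or
- the Kaplan-Meier 12-month cumulative incidence per group with 95% CI, using the same censoring rule.

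State the denominator of the crude percentage and describe it as the observed proportion, so that the 12-month incidence statement rests on the adjusted estimate. Keep simple percentages for the 30-minute, 0-7 day and roughly 28-30 day endpoints.

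The cost is one extra table. The dates are already required: SAE onset in section 8.3, and visit dates and the date of completion in sections 11.8 and 12.2. The stated incidence will be slightly higher. If loss is related to risk, which is possible because section 5.1.3 includes intolerable adverse events and health status among the withdrawal grounds, the added estimate corrects the bias only in part. The report should say so.

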### **3.1. Primary Objectives**

1. To compare the immunogenicity (prototype SARS-CoV-2 Omicron variant stain) of NVSI-06-09 vaccine with Vero Cell vaccine, 14 days after a single dose of the booster vaccine in adults  $\geq 18$  years of age.
2. To compare the safety of NVSI-06-09 vaccine with Vero Cell vaccine, 28 days after a single dose of the booster vaccine in adults  $\geq 18$  years of age.

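### The primary safety comparison is fixed as Fisher exact tests with no effect estimate or interval, in a trial sized only on antibody titres, so for rare events a non-significant result says little

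*Protocol*

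**What the plan says.** Protocol section 3.1 makes safety the second primary objective: "To compare the safety of NVSI-06-09 vaccine with Vero Cell vaccine, 28 days after a single dose of the booster vaccine". Among the primary endpoints in section 4.3, the first is immunogenicity and the other four are adverse-event incidences over successive windows. The last of them reads "The incidence of SAE and AESI observed after vaccination and up to 12 months after full course of immunization".

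Section 10.3.4 sets out the safety analysis. For all, related, unrelated, Grade 3 or above, and related Grade 3 or above treatment-emergent events, and again for serious events, it says "The frequency, participants and percentage in each group will be reported" and then "Fisher exact test will be used to compare the difference between the groups". It adds MedDRA summaries, a split into solicited and unsolicited events, onset and severity summaries, and listings. It names no risk difference, confidence interval or margin for any safety endpoint, and no between-group comparison for AESIs.

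Section 10.3.3, on immunogenicity, does specify a between-group difference and a GMT ratio with 95% CIs. Section 4.4 states hypotheses and margins for immunogenicity only.

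Section 10.1 bases the sample size on GMT alone and closes with "Based on the above considerations and the drop-out rate, it is planned to enroll 516 participants". Section 4.2 allocates these 1:1, "with 258 participants in each booster group". The Safety Set in section 10.2 is defined by vaccination: "It includes all participants who receive one dose of booster vaccination".

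**The concern.** A Fisher test asks whether the data contradict equal risk. It does not say how large a difference remains plausible. For a comparative primary objective, the size of the difference and its uncertainty are what the reader needs, and the protocol supplies both for antibody titres but not for safety.

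The trial was never sized for a safety difference, so whether the test reaches significance on an uncommon event depends mainly on the event rate and on 258 per group. If a p-value is the only inferential output, a non-significant result on SAEs or severe events looks much the same whether the new vaccine carries no excess risk or a twofold one.

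**Working it through.** **1. The plan's own sample size.** Inputs from section 10.1: non-inferiority margin 0.17609 on the log10 scale, true difference 0, SD 0.55, one-sided alpha 0.025, power 0.90, 20% drop-out.

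n per group = 2 × SD² × (z₀.₉₇₅ + z₀.₉₀)² / margin² = 2 × 0.55² × (1.960 + 1.282)² / 0.17609² = 205.01, rounded up to 206.

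With drop-out: 206 / 0.8 = 257.5, so 258 per group and 516 in total. The plan's figures reproduce, and no safety quantity enters the calculation.

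**2. Inputs for the safety test.**
- Group size: 258, because the Safety Set counts everyone vaccinated. This assumes that all randomized participants are vaccinated.
- Test level: two-sided 5%. The protocol gives none for the Fisher tests, so this is an assumption.
- Control event rate: not given anywhere in the protocol, so it is assumed and varied from 0.5% to 5%.

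**3. Exact power.** Let X and Y be independent Binomial(258, p₁) and Binomial(258, p₀) event counts. Power is the sum of P(X = x) × P(Y = y) over all tables (x, y) with two-sided Fisher p ≤ 0.05, by full enumeration. The chance of missing the difference is 1 minus power.

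| Assumed control rate | Doubling missed | Tripling missed |
|---|---|---|
| 0.5% | 98.5% | 93.0% |
| 1% | 92.9% | 75.0% |
| 1.5% | 87.4% | 57.7% |
| 2% | 81.4% | 42.0% |
| 3% | 69.3% | 20.6% |
| 4% | 58.0% | 8.8% |
| 5% | 47.2% | 3.5% |

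For a common event the test does better: 20% against 30% has 72% power.

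**4. What the p-value hides and an interval shows.** Suppose 10 of 258 have an event on NVSI-06-09 and 5 of 258 on Vero Cell, an observed doubling.
- Fisher p = 0.29.
- Risk difference = 10/258 − 5/258 = 1.94 percentage points, with a Newcombe 95% CI of −1.1 to +5.2 points.

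The p-value alone may sound reassuring. The interval shows that an excess of about 5 points is still compatible with the data.

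**5. Very rare events.** Five events against none gives p = 0.061, and six against none gives p = 0.030, so at least six against none are needed for significance. No events among 258 still allows a true rate of up to 1 − 0.025^(1/258) = 1.42% (upper limit of the exact two-sided 95% CI).

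**The case against.** The strongest case against is that nothing here is wrong as written. Fisher's test is valid for sparse counts, and the protocol reports counts and percentages from which anyone could compute an interval. The choice of interval method is commonly left to a statistical analysis plan, which is not shown. Low power for rare events comes with any trial of 516 sized on titres, and adding intervals does not change it.

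Much of this stands. A missing interval would not be a finding on its own, and the remedy adds no power. What remains is that the protocol does make a choice: it fixes a test of no difference as the inferential answer to a primary comparative objective, while specifying estimates with intervals for the other primary objective.

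Three stronger readings are tempting, and the document does not support them.
- A reader might infer that the plan will treat a non-significant result as comparable safety. No passage says so. The objective is to compare, and there is no safety hypothesis or decision rule.
- A reader might take 75% to 93% as the miss rate of the design. It belongs to an assumed 1% control rate. That may suit rare SAEs, but it is not established for Grade 3 or above events. A tripling from 5% to 15% is missed only 3.5% of the time; 15% is also the level in the suspension criterion for Grade 3 or above reactions, which is a trigger and not an expected rate.
- A reader might think that the Fisher test fails for AESIs. Section 10.3.4 plans no Fisher test for AESIs at all.

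**Conclusion.** The point holds as a matter of analysis choice, and it should be changed. Safety is a primary comparison, but its only named between-group analysis is a null-hypothesis test without an estimate, in a sample never sized for it. At an assumed 1% control rate the power is about 7% for a doubling and 25% for a tripling. Across assumed control rates of 0.5% to 5%, a doubling is missed 47% to 99% of the time; for a tripling the range runs from 93% down to 3.5%, so the weakness is confined to uncommon events and moderate excesses.

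These figures rest on assumed event rates, a two-sided 5% level and full vaccination of 258 per group. The risk is that non-significance could be misread, not that the protocol prescribes the misreading.

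**What to change.** In section 10.3.4, make the between-group result for each primary safety endpoint the risk difference (NVSI-06-09 minus Vero Cell) with a two-sided 95% CI by the Miettinen-Nurminen or Newcombe method. Cover any, related and Grade 3 or above treatment-emergent events, solicited events on days 0 to 7, SAEs, and AESIs, for which no comparison is now named. Add an exact (Clopper-Pearson) 95% CI for the incidence in each group, including where the count is zero.

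Keep the Fisher p-value as descriptive, and state that a non-significant result is not evidence of similar safety. Do not tie the safety conclusion to the upper confidence bound: no margin is set, so such a statement would define no rule.

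The cost is some wording and a few more columns in the safety tables. The upper bounds for rare events will look less reassuring than a non-significant p-value.
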